#### 4.5 measures to reduce bias

##### 4.5.1 Randomization and Allocation

Randomization in this study is done to test the feasibility of randomization for the main confirmatory study. That is, randomization is not done with the aim of testing comparative hypotheses.

The randomization code is created by an independent person from the Institute of Social Medicine, Epidemiology and Health Economics (who is not otherwise involved in the study) as a block randomization (with variable block length) stratified by study center (general practitioner's practice) with an allocation ratio of 2:1.

All patients who consent to participate and meet the inclusion criteria will be randomized after the baseline assessment. The randomization codes will be taken from the REDCap database by the study

|                                  |                                   |                                                                                                         |                 |
|----------------------------------|-----------------------------------|---------------------------------------------------------------------------------------------------------|-----------------|
| Version: V1.2                    | Last review:
February 12, 2025 | Created: [name], [name], [name], [name], [name] | Page
22of 52 |
|                                  |                                   | Reviewed by: [name], [name]                                                    |                 |
| Release on:
February 12, 2025 | Next check:
N/A                | Released: [name]                                                                       |                 |
|                                  |                                   | Valid from: 04.09.2024                                                                                  |                 |

|                   |                          |                                                                 |  |
|-------------------|--------------------------|-----------------------------------------------------------------|--|
| study
protocol | Study: „Soziales Rezept“ | Campus:
CCM                                                  |  |
|                   |                          | Scope:
Institute for General Practice and
Family Medicine |  |

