#### 4.5.2 blinding

Due to the study design, blinding of the investigators , link workers and patients is not possible. Due to the 2:1 randomization, blinding of the statistical analyses is also not possible.

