### 8.2 case number estimate

Since this is an exploratory feasibility study without confirmatory hypothesis testing, no formal sample size calculation will be performed. Based on previous experience, we assume that the analysis of a total of 215 participants (in a ratio of 2:1: 143 in the SP arm and 72 in the TAU+ arm) is sufficient to descriptively determine the feasibility and acceptability aspects of the study and to obtain further information for planning the subsequent study.

A drop-out of approximately 30% is expected, so that follow-up data for secondary clinical endpoints of 150 patients (n = 100 in the SP arm and n = 50 in the TAU+ arm) will be available after 6 months.

|                                  |                                   |                                                                                                         |                  |
|----------------------------------|-----------------------------------|---------------------------------------------------------------------------------------------------------|------------------|
| Version: V1.2                    | Last review:
February 12, 2025 | Created: [name], [name], [name], [name], [name] | Page
33 of 52 |
|                                  |                                   | Reviewed by: [name], [name]                                                    |                  |
| Release on:
February 12, 2025 | Next check:
N/A                | Released: [name]                                                                       |                  |
|                                  |                                   | Valid from: 04.09.2024                                                                                  |                  |

|                   |                          |                                                                 |  |
|-------------------|--------------------------|-----------------------------------------------------------------|--|
| study
protocol | Study: „Soziales Rezept“ | Campus:
CCM                                                  |  |
|                   |                          | Scope:
Institute for General Practice and
Family Medicine |  |

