### 8.4 analyses

Primary endpoints: The proportion of participants in the intervention group who attended at least one appointment with the link worker and the proportion of participants who discontinued the study before the 6-month follow-up (dropout rate) will be analyzed descriptively, with frequencies and percentages, including 95% confidence intervals per treatment group. The comparison of the dropout rate between the treatment groups will be done descriptively and using logistic regression to determine possible influencing factors.

Secondary endpoints are analyzed descriptively (frequencies/percentages, mean/standard deviation or median/interquartile depending on scale and distribution, each with corresponding 95% confidence intervals).

Comparisons between treatment groups will be performed using logistic regression (binary endpoints) or analysis of covariance (continuous endpoints adjusted for baseline , if available), taking center into account.

Safety: Adverse events are analyzed descriptively (frequencies and percentages per treatment group).

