### 8.5 sensitivity analyses

Relevant endpoints will additionally be analyzed using the per-protocol population.

Subgroup analyses are carried out for relevant endpoints. The following subgroups are used, among others:

- Gender
- underlying psychosocial problem(s)
- age groups.

|                                  |                                   |                                                                                                         |                  |
|----------------------------------|-----------------------------------|---------------------------------------------------------------------------------------------------------|------------------|
| Version: V1.2                    | Last review:
February 12, 2025 | Created: [name], [name], [name], [name], [name] | Page
34 of 52 |
|                                  |                                   | Reviewed by: [name], [name]                                                    |                  |
| Release on:
February 12, 2025 | Next check:
N/A                | Released: [name]                                                                       |                  |
|                                  |                                   | Valid from: 04.09.2024                                                                                  |                  |

|                   |                          |                                                                 |  |
|-------------------|--------------------------|-----------------------------------------------------------------|--|
| study
protocol | Study: „Soziales Rezept“ | Campus:
CCM                                                  |  |
|                   |                          | Scope:
Institute for General Practice and
Family Medicine |  |

This is also done descriptively and with logistic regression or analysis of covariance with an additional factor interaction (treatment group\*subgroup) in the model. Details of the definitions of the subgroups are described in the SAP.

If there are relevant differences between the groups at baseline, these variables are additionally adjusted.

Clustering by center/physician or link worker is taken into account with different models (e.g. fixed/random effects).

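### The 8.5 sensitivity analysis picks extra covariates because the arms differ at baseline, not because the covariates predict the outcome

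*Protocol*

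**What the plan says.** The rule stands in protocol Section 8.5, headed "8.5 sensitivity analyses": "If there are relevant differences between the groups at baseline, these variables are additionally adjusted". The wording is an instruction, and its trigger is a difference between the arms. A relation to the outcome is not asked for.

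The main group comparisons are set in Section 8.4: logistic regression for binary endpoints and, for continuous ones, "analysis of covariance (continuous endpoints adjusted for baseline , if available), taking center into account". Their covariates are therefore fixed in advance.

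Section 4.5.1 describes concealed block randomisation, "stratified by study center (general practitioner's practice) with an allocation ratio of 2:1". Section 8.2 plans 215 randomised patients, "in a ratio of 2:1: 143 in the SP arm and 72 in the TAU+ arm". Section 8.1 treats all results as exploratory and leaves details of the sensitivity analyses to the SAP.

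**The concern.** With concealed randomisation, a baseline difference among randomised patients outside the stratification factor arises by chance. Its size says nothing about whether the variable predicts the outcome. A variable unrelated to the outcome needs no adjustment even if it differs. A strong predictor is worth including even if it is balanced, because it reduces residual variance. A rule keyed to imbalance can get both cases wrong.

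It also lets the data choose the model, so the nominal error rate of the sensitivity analysis need not hold. A sensitivity analysis is easiest to interpret when its model was settled beforehand.

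The study's purpose is to inform a confirmatory trial, including its sample size (Section 3), and a publication on clinical efficacy is planned (Section 16). Adjusted estimates and residual variances may feed into both, and they should not depend on which variables happened to differ.

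**Working it through.** **1. The plan's own sample size.** Section 8.2 expects about 30% dropout and 6-month data on about 150 patients.
- 150 / 0.70 = 214.3, rounded up to 215. Split 2:1, 215 × 2/3 = 143.3 and 215 / 3 = 71.7, giving 143 and 72.
- Forward: 143 × 0.70 = 100.1 and 72 × 0.70 = 50.4, which agrees with "n = 100 in the SP arm and n = 50 in the TAU+ arm".

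These figures reproduce and are not in dispute.

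**2. Chance that one variable triggers.** For a standardised mean difference (SMD) between randomised arms, SE = √(1/n₁ + 1/n₂), and the chance of exceeding a threshold t is 2 × [1 − Φ(t/SE)].
- 143 vs 72: SE = √(1/143 + 1/72) = 0.1445.
- t = 0.2: 0.2/0.1445 = 1.384, probability 0.166.
- t = 0.5: 0.5/0.1445 = 3.46, probability 0.0005.
- A p < 0.05 rule: 0.05 by construction.

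**3. Chance that at least one of m variables triggers**, if independent: 1 − (1 − p)^m. The protocol gives neither a threshold nor a count, so both are assumptions. Section 6.4 names six sociodemographic items as examples, plus long-term diagnoses, and Table 4 adds eight baseline instruments. That makes 15; I use 10 and 15, with 7 to 30 as the range.

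| Meaning of 'relevant' (143 vs 72) | m = 10 | m = 15 | m = 7 to 30 |
|---|---|---|---|
| SMD > 0.2 | 84% | 93.5% | 72% to 99.6% |
| SMD > 0.25 | 58% | 73% | 46% to 93% |
| p < 0.05 | 40% | 54% | 30% to 79% |
| SMD > 0.5 | 0.5% | 0.8% | 0.4% to 1.6% |

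Correlation between variables lowers these. With m = 15 and pairwise correlation 0.5, simulation gives 79% for SMD > 0.2 and 36% for p < 0.05. If balance is judged in the 100 vs 50 expected to have 6-month data, SE = √(1/100 + 1/50) = 0.173, and 15 independent variables give 98.6% for SMD > 0.2, 54% for p < 0.05 and 5.7% for SMD > 0.5.

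**4. Effect on the sensitivity estimate.** Illustrative null simulation, 6,000 trials of 100 vs 50. All inputs are assumptions: 15 independent standard normal candidates, three of them prognostic (coefficients 0.3, 0.3, 0.2), baseline value of the outcome with coefficient 0.5, residual SD 0.75, trigger SMD > 0.2. Centre was not modelled.

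| Model | Type I error | SD of estimate |
|---|---|---|
| Baseline value only | 5.1% | 0.154 |
| Plus variables that triggered | 3.8% | 0.144 |
| Plus the three prognostic variables, fixed in advance | 5.1% | 0.132 |

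The Monte Carlo standard error at 5% is √(0.05 × 0.95 / 6000) = 0.28 percentage points, so 3.8% is a real departure, in the conservative direction. Against the prespecified set, the imbalance rule has (0.144/0.132)² = 1.19 times the variance.

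**The case against.** **Scope.** The rule is a sensitivity analysis added to main models whose covariates are already fixed, in an exploratory study where randomisation does not serve to test comparative hypotheses (Section 4.5.1). A reader might infer that all adjusted estimates become a moving target. The text does not support that. The 8.4 comparisons do not use the rule, and neither do the proportions with 95% confidence intervals for the two primary endpoints. This stands and limits the consequence.

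**Frequency.** A reader might also infer that the rule will almost always trigger. That cannot be shown while the meaning of 'relevant' is open: the table runs from about 1% to over 90% for the same 15 variables.

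**Direction of harm.** It is tempting to read a false-positive risk into the rule. The simulation shows the opposite, and the triggered model was even more precise than the baseline-only model (0.144 vs 0.154). The loss is relative to covariates chosen in advance as prognostic, under assumed effects.

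**Blinding.** Section 4.5.2 says: "Due to the 2:1 randomization, blinding of the statistical analyses is also not possible". One might infer that analysts will choose covariates with the results in view. The protocol does not say so. Any baseline comparison by arm needs the grouping, and 8.1 puts the SAP before data analysis.

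**SAP.** The threshold and candidate list may be in the SAP, so their absence here is no fault. An SAP could also read 'relevant' to include prognostic relevance. But an SAP that follows the sentence would still make a baseline difference the condition for adjusting, so a balanced predictor would still be left out.

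**Dropout.** This is the best argument for the rule. Section 8.2 says: "A drop-out of approximately 30% is expected"; missing data are not imputed (8.3), and loss in the control arm is a stated concern (4.2). If 'groups' means the patients analysed, differences may reflect differential dropout, and adjusting for them is a sensible check. That supports adjusting for predictors of outcome and dropout. It does not support waiting for an imbalance before naming them.

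**Conclusion.** The point holds for the sensitivity analysis of 8.5. The protocol fixes a selection principle based on imbalance where one based on prognosis is available at almost no cost. The consequence is modest: a sensitivity model that depends on the data, a nominal error rate somewhat off (3.8% against 5%, conservative), and about 19% more variance than a prespecified prognostic set in the simulated setting. Under common thresholds the rule would often act: about 84–94% for SMD > 0.2 and 40–54% for p < 0.05 with 10 to 15 independent variables at 143 vs 72. Under a threshold of SMD > 0.5 it would hardly ever act (about 1% with 15 variables).

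The trigger rates rest on the assumed threshold, number and independence of variables. The error rate and precision rest on the simulation's assumed effects. That the rule selects on imbalance rests on none of these.

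**What to change.** Replace the sentence in 8.5 with a sensitivity model that keeps the 8.4 covariates (baseline value of the endpoint where available, and centre) and adds a short set of prognostic variables named before data analysis. Age and gender are candidates. The number of social problems could be added if it is judged prognostic of outcome or dropout and is recorded in both arms before randomisation. State that baseline differences are described in the baseline table and do not determine the model, and carry the same list into the SAP.

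The cost is one sentence in the protocol and a matching line in the SAP. No new data are needed: 8.5 already uses gender, age groups and the underlying problems as subgroups. The downside is that a chance imbalance in a variable not on the list will be reported but not adjusted for.

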## 9 data management

Data management is carried out in accordance with the specifications of the quality management manual of the Institute for Social Medicine, Epidemiology and Health Economics. The data is only stored and processed for the respective purpose. The applicable data protection laws are observed.

### 9.1 collection and storage of data

In the consent form to participate in the study, the study participant agrees to the recording, processing and storage of his/her personal and medical data as part of this survey.

The data collected as part of the study are recorded and stored in the REDCap online database ( REDCap = Research Electronic Data Capture, version 14.0 or higher). The REDCap used to collect the data runs on virtual machines in the Charité IT infrastructure. The REDCap web server ( accessible via <https://redcap.charite.de> ) is located in the so-called DMZ ( demilitarized zone ) behind a firewall.

Personally identifiable data ( PiD ) are entered into REDCap by the practice staff . The research data (FD) are collected and stored separately from the PiD in another independent REDCap project; no PiD is transmitted to the survey project.

The databases are only accessible to data management and authorized study personnel with individualized login via 2-factor authentication.

The study data and study documents will be archived for 10 years after the end of the study and all personally identifiable documents and data will then be deleted. All research data will be anonymized 10 years after the end of the study.

|                                  |                                   |                                                                                                         |                  |
|----------------------------------|-----------------------------------|---------------------------------------------------------------------------------------------------------|------------------|
| Version: V1.2                    | Last review:
February 12, 2025 | Created: [name], [name], [name], [name], [name] | Page
35 of 52 |
|                                  |                                   | Reviewed by: [name], [name]                                                    |                  |
| Release on:
February 12, 2025 | Next check:
N/A                | Released: [name]                                                                       |                  |
|                                  |                                   | Valid from: 04.09.2024                                                                                  |                  |

|                |                          |                                                              |  |
|----------------|--------------------------|--------------------------------------------------------------|--|
| study protocol | Study: „Soziales Rezept“ | Campus:
CCM                                               |  |
|                |                          | Scope:
Institute for General Practice and Family Medicine |  |

## 9.2 pseudonymization

The data are recorded in REDCap using pseudonyms, which consist of consecutive numbers without initials or birth dates of the participants. The PiD database is the re-identification list for the pseudonymized FD entered by the study staff in REDCap .

## 9.3 Rights of participants (revocation, data deletion, right to information, correction)

Participants can object to further processing of their data at any time.

Participants have the right to request the immediate deletion of the data collected about them as part of the study.

There is a right to information about all study data collected. Participants have the right to information about and correction of study data collected about them at any time.

## 10 Qualitative process evaluation

The study is complemented by a qualitative process evaluation in which semi-structured episodic interviews are conducted with stakeholders involved in the study ( patients, general practitioners , representatives of local services and members of the study team).

### 10.1 Goals and Topics of Qualitative Process Evaluation

Table 5 presents the objectives and topics of the qualitative process evaluation.

*Table 5: Objectives and topics of qualitative process evaluation*

| Objectives Qualitative Process Evaluation                                                                                                                                                                               | Topics Qualitative Process Evaluation                                         | each for:                       |
|-------------------------------------------------------------------------------------------------------------------------------------------------------------------------------------------------------------------------|-------------------------------------------------------------------------------|---------------------------------|
| The qualitative semi-structured episodic interviews are intended to present the perspectives of the actors involved ( patients, general practitioners , link workers and representatives of local services) in order to | Acceptance of study procedures (including randomization) and the intervention | patients                        |
|                                                                                                                                                                                                                         |                                                                               | family doctors                  |
|                                                                                                                                                                                                                         |                                                                               | Link Worker                     |
|                                                                                                                                                                                                                         |                                                                               | representatives of local offers |
|                                                                                                                                                                                                                         |                                                                               | study team                      |

|                                  |                                   |                                                                                                         |                  |
|----------------------------------|-----------------------------------|---------------------------------------------------------------------------------------------------------|------------------|
| Version: V1.2                    | Last review:
February 12, 2025 | Created: [name], [name], [name], [name], [name] | Page
36 of 52 |
|                                  |                                   | Reviewed by: [name], [name]                                                    |                  |
| Release on:
February 12, 2025 | Next check:
N/A                | Released: [name]                                                                       |                  |
|                                  |                                   | Valid from: 04.09.2024                                                                                  |                  |

|                   |                          |                                                                 |  |
|-------------------|--------------------------|-----------------------------------------------------------------|--|
| study
protocol | Study: „Soziales Rezept“ | Campus:
CCM                                                  |  |
|                   |                          | Scope:
Institute for General Practice and
Family Medicine |  |

|                                                                                                                                                  |                                                      |                                 |
|--------------------------------------------------------------------------------------------------------------------------------------------------|------------------------------------------------------|---------------------------------|
| qualitatively assess the feasibility of the study, gain insights for future studies and care services and identify indications of contamination. | Practicability of study procedures and intervention  | patients                        |
|                                                                                                                                                  |                                                      | family doctors                  |
|                                                                                                                                                  |                                                      | Link Worker                     |
|                                                                                                                                                  |                                                      | representatives of local offers |
|                                                                                                                                                  |                                                      | study team                      |
|                                                                                                                                                  | Need for and use of the intervention                 | patients                        |
|                                                                                                                                                  |                                                      | family doctors                  |
|                                                                                                                                                  |                                                      | Link Worker                     |
|                                                                                                                                                  |                                                      | representatives of local offers |
|                                                                                                                                                  |                                                      | study team                      |
|                                                                                                                                                  | Potential for the implementation of the intervention | patients (intervention arm)     |
|                                                                                                                                                  |                                                      | family doctors                  |
|                                                                                                                                                  |                                                      | Link Worker                     |
|                                                                                                                                                  |                                                      | representatives of local offers |
|                                                                                                                                                  |                                                      | study team                      |
|                                                                                                                                                  | hurdles to the implementation of the intervention    | patients (intervention arm)     |
|                                                                                                                                                  |                                                      | family doctors                  |
|                                                                                                                                                  |                                                      | Link Worker                     |
|                                                                                                                                                  |                                                      | representatives of local offers |

|                                  |                                   |                                                                                                         |                  |
|----------------------------------|-----------------------------------|---------------------------------------------------------------------------------------------------------|------------------|
| Version: V1.2                    | Last review:
February 12, 2025 | Created: [name], [name], [name], [name], [name] | Page
37 of 52 |
|                                  |                                   | Reviewed by: [name], [name]                                                    |                  |
| Release on:
February 12, 2025 | Next check:
N/A                | Released: [name]                                                                       |                  |
|                                  |                                   | Valid from: 04.09.2024                                                                                  |                  |

|                |                          |                                                              |  |
|----------------|--------------------------|--------------------------------------------------------------|--|
| study protocol | Study: „Soziales Rezept“ | Campus:
CCM                                               |  |
|                |                          | Scope:
Institute for General Practice and Family Medicine |  |

|  |                                           |            |
|--|-------------------------------------------|------------|
|  |                                           | study team |
|  | feeling of being part of the neighborhood | patients   |

